### Randomization and Blinding

Practices will be randomized in a ratio of 1:1 to intervention or control using stratified block randomization [31] based on practice patient list size using a Keele CTU computer-generated random sequence and concealment by ensuring that each practice has an anonymized code. The randomization sequence and stratification will be carried out by the senior trial statistician. The block randomization will follow Keele CTU’s randomization SOP, and the data sequence will be held on a secure server. Blinding for individual clinicians is not possible, but any staff involved in the collection or database entry of patients’ outcome data will be blind to allocation. Access to the allocation sequence will be restricted to those with authorization. Allocation will be shared with the study team (except for the trial statistician and data entry staff who are to remain blind) who will then arrange to inform each practice about their allocation. Data cleaning/checking through stage 1 *data-freeze* and stage 2 *data-lock* reviews will be carried out by the trial statistician, thus maintaining blinding to allocation. The TSC will also be blinded to allocation unless it becomes absolutely necessary to reveal allocation. The DMC trial statistician will be involved in the allocation assignment and, therefore, will not be blinded throughout the study. These processes follow recommendations for cluster trials [26] to reduce selection bias where randomization is before patient data collection.

### Interventions

#### Practice Recruitment Template Installation

Following confirmation that a practice is eligible and willing to take part, an initial setup meeting will be held between the practice, study research team, and a CRN member. This will take place for all practices in both arms of the trial and will be followed by training sessions where the computer template will be installed and demonstrated on the practice’s EMIS clinical system. Once the template is installed, the practice is *live*, and potentially eligible participants will be identified in consultations.

### Intervention Arm

The recommended matched clinical management options are not new but summarize available evidence-based options into those considered by expert consensus to be appropriate for patients at low, medium, and high risk of persistent pain and disability.

The Start MSK stratified care approach has 2 components: (1) prognostic tool and (2) matched options.

#### Prognostic Tool

The Keele Start MSK Tool (clinician-completed version) is freely available [32]; is used in the patient consultation [21]; and is supported by an embedded template in the practice’s computer system, dedicated training and support sessions, regular audits, peer feedback, and clinical mentoring opportunities using an evidence-based clinician support package to support clinician behavior change [33]. The prognostic tool has 10 questions from which the patient’s score and subgroup (low, medium, or high risk of persistent pain and disability) are calculated.

#### Matched Options

Appropriate matched clinical management options based on an individual’s prognosis on the Keele Start MSK Tool will be displayed to support clinical decision making. The matched clinical management options were identified by an evidence synthesis [22], followed by 3 expert consensus workshops [23], during an earlier phase of research, and then further refined following the Start MSK feasibility and pilot [21].

### Per Protocol Treatment Decision Rules

Patients at low risk will be considered to be treated *per protocol* if they receive only treatment options 1 or 2 (Figure 3). Patients at medium risk will be *per protocol* if they receive any of options 3-6 (although option 5 is for specific pain sites only). Patients at high risk will be *per protocol* if they receive option 3 or any options between 7 and 11.

**Figure 3 figure3:**
[figure not shown]
Recommended matched treatment options. GP: general practice; MSK: musculoskeletal; NSAIDS: Nonsteroidal anti-inflammatory drugs.

The matched options for patients at low risk include advice and education (using printed materials where possible), over-the-counter analgesics, and avoidance of MSK investigations and referrals (where possible). Matched options for patients at medium risk, in addition to the low-risk options, include GPs being encouraged to refer patients to physiotherapy, to review their pain medication, and to consider investigations where necessary. Matched options for patients at high risk, in addition to the medium- and low-risk options, include prescription of atypical analgesia if neuropathic pain is present; referral to specialist services (eg, orthopedics, rheumatology, and pain clinics); imaging; and/or booked reviews to manage complex clinical factors such as comorbidities, polypharmacy, and frailty.

### Clinician Support for Delivering Stratified Care

The training and support sessions provided to intervention and control clinicians are designed to equip them with the knowledge and skills to complete the study recruitment template and understand the study inclusion/exclusion criteria. In addition, for intervention practices, a 2-hour intervention training session will be provided. This includes learning about previous stratified care research [19,20], the rationale for developing this new intervention, and investigating whether it will benefit patients with a broader range of MSK pain. Training will describe the aim to reduce unnecessary health care for patients at low risk, while better targeting health care resources for patients at medium or high risk. Clinicians will have a demonstration of how to use the new approach and have the opportunity to try it out and ask questions and explore how it can be integrated into routine practice. The session will also include discussion and clarification about how the approach differs from usual care and each of the recommended clinical management options. We will also invite a representative from the local MSK physiotherapy service to the training sessions and discuss how best to ensure that patient referrals to physiotherapy include a record of the index consultation and the patient’s Start MSK Tool risk group and determine the best method for physiotherapists to communicate with referring GPs if they are concerned about the patient. A feedback meeting will be held with all participating practices (intervention and control) roughly 6 weeks after starting recruitment to discuss the report of their use and completion of the study-specific IT template. For intervention practices, additional feedback on their fidelity to the recommended matched clinical management options will also be provided, comparing each clinician with their colleagues in the same practice and with other clinicians in the trial (anonymized). Monthly email feedback reports will be sent to participating practices.

Physiotherapists linked to intervention practices will also have the opportunity to attend a short training session about the trial and be required to avoid treating patients from control practices for the period of the trial to avoid contamination. However, other key features of physiotherapy care will be as similar as possible for patients irrespective of whether they come from intervention or control practices, including physiotherapy waiting times, treatment session length and number, and the clinical grade of the treating therapist. We will collect these process data from physiotherapy services using a mix of usual clinical record data and standardized case report forms for the study.

### Control Arm

In the usual care control arm, patients who consult at their general practice will be assessed and receive advice and treatment as usual (eg, advice and education; medication; referral for investigations or tests; or referral to other services such as physiotherapy, MSK interface clinics, or secondary care specialists such as orthopedics and rheumatology), without the use of formal stratification tools. To keep the control arm as close to *usual care* as possible, clinicians will be advised to follow their usual approach for responding to a patient’s pain intensity rating for the presenting MSK problem. Asking a patient the intensity of their pain and where their pain is coming from is common practice [30] and therefore should have little impact on the *usual care* provided.

### Data Collection

There will be 3 different types of data collection:

1. Individual patient data, collected from:

The practices’ completed computer templates at the point of consultationInitial and 6-month postal questionnaires to participants (full and minimum data versions)Monthly SMS text or 1-page postal questionnaire.

2. Clinician decision making and behaviors using data collected from medical records and case report forms

3. Practice-level anonymized aggregated data of MSK Read codes and template use.

### Individual Patient Outcomes

#### General Practice Information Technology Template

The first item on the template asks the primary care clinician to confirm if their patient gives consent to have their contact details shared with the research team. If the answer is yes, then the clinician will record the location of the patient’s MSK pain. How this is answered determines which study letter and questionnaire the patient will be sent, as these are slightly different for patients with back, neck, knee, shoulder, or multisite pain. The item reads “Please confirm the primary pain site the patient is consulting with today.” Possible response options include *back pain*, neck pain, *knee pain*, *shoulder pain*, *multisite pain*, or *unable to complete template* (which leads to the exit screen). The third question on the template asks the clinician to record the patient’s MSK pain intensity by asking “How intense was your pain, on average, over the last 2 weeks?” (Responses are recorded on a scale of 0-10, where 0 is *no pain* and 10 is *worst pain ever*.)

#### Initial and 6-Month Follow-Up Questionnaires

The initial and 6-month follow-up postal questionnaires are designed to collect information on descriptive characteristics of the participants, pain-related characteristics, and primary and secondary outcome measures (see Table 1 below). Patients are informed in their study invitation that they have been contacted because they recently visited their general practice (the date of their visit will be given) for their MSK pain, which will be prepopulated in the letter (eg, knee pain, shoulder pain) using information from weekly downloaded template codes.

Participants will also be told that it is important they think about their *MSK pain* as they answer the following question: “Thinking about your (eg, neck) pain: Over the last 2 weeks, on average, how intense was your pain?” (Responses were recorded on a scale of 0-10, where 0 is *no pain* and 10 is *worst pain ever*.)

**Table 1 table1:** A summary of patient-reported data collected.

Conceptual domain		Operational definition	Empirical measure	Number of items	Time
**Primary outcome**					
	Pain intensity	Usual pain intensity	NRS^a^ 0-10	1	GPT^b^, I^c^, 6FU^d^, MF^e^, and MDC^f^
**Secondary outcomes**					
	Risk status—Start MSK^g^ Tool	Risk of persistent disabling pain	Yes/no	9	I and 6FU
	MSK health	Impact from MSK symptoms	MSK-HQ^h^, 5-point Likert scale	14	I and 6FU
	Overall rating of change	Change since MSK pain consultation	−5 to +5 scale	1	I and 6FU
	Physical activity level	Days past week of moderate activity	1-7 days	1	I and 6FU
	Fear-avoidance beliefs	Fear of movement	Tampa Scale of Kinesiophobia-11	11	I and 6FU
	Satisfaction	Satisfaction with care	5-point Likert scale	1	I and 6FU
	Perceived reassurance from general practitioner consultation	Patient-perceived reassurance 4 subscales: information gathering, relationship building, generic reassurance, and cognitive reassurance	12 items with 7-point Likert scale	12	I
	Receipt of written education material from general practitioner	Single item to ask if patient received written information at their general practitioner visit	Yes/no/don’t remember	1	I
	Pain self-efficacy	Single item: confidence to manage pain	NRS 0-10	1	I and MF
	Psychological distress	Single item regarding level of distress	NRS 0-10	1	I and MF
**Site-specific function depending on MSK pain site**					
	Back pain function	Physical function	RMDQ^i^ – original version	24	I and 6FU
	Neck pain function	Physical function	NDI^j^	10	I and 6FU
	Shoulder pain function	Physical function	SPADI^k^	13	I and 6FU
	Knee pain function	Physical function	KOOS-PS^l^	7	I and 6FU
	Multisite pain function	Physical function	SF-12 PCS^m^	12	I and 6FU
**Quality of life measures**					
	Health-related quality of life	Utility-based quality of life	EuroQol-5D	5	I, 6FU, and MDC
**Health care costs**					
	Health care resource use	Use of primary care, other National Health Service services, and private health care	Yes/no and if yes details of resources used	3	6FU
	Performance at work	How productivity at work is affected	NRS 0-10	1	I and 6FU
	Absenteeism from work	Number of days absent from work	Yes/no and details	1	I and 6FU
**Patient descriptors**					
	Age	Age at MSK consultation	Date of birth	1	GP T
	Sex	Sex	Male/female	1	GP T
	Employment status and absence from work	Employment status at time of questionnaire	Yes/no and details	1	I and 6FU
	Socioeconomic status	The individual’s current or most recent job title	Job title: categorized as manual/nonmanual	2	I
	MSK pain location	Site of MSK pain complaint	Choice of anatomical region	1	GP T
	Episode duration	Time since last whole month pain free	Episode duration	1	I
	Health literacy screen	Health literacy	Single question: Likert scale	1	I
	Comorbidities	Other diagnosed comorbidities to select from a list	Yes	1	I
	Support needed	Who has completed the questionnaire	Patient/carer/staff/other	1	I
	Living arrangements	Lives alone	Yes/no	1	I
	Previous episodes	Number of previous pain episodes	Number	1	I

^a^NRS: numerical rating scale.

^b^GP T: GP template.

^c^I: initial questionnaire.

^d^6FU: 6-month follow-up.

^e^MF: monthly follow-up.

^f^MDC: minimal data collection.

^g^MSK: musculoskeletal.

^h^MSK HQ: Musculoskeletal Health Questionnaire.

^i^RMDQ: Roland-Morris Disability Questionnaire.

^j^NDI: Neck Disability Index.

^k^SPADI: Shoulder Pain and Disability Index.

^l^KOOS-PS: Knee Injury and Osteoarthritis Outcome Score-Physical Function Shortform.

^m^SF-12 PCS: Short-Form 12 Physical Component Scale.

#### Monthly SMS Text or 1-Page Questionnaire for 3 Items, Including the Primary Outcome

In addition to the primary outcome (pain intensity), the monthly SMS text or 1-page questionnaire includes 2 potential mediating variables using the following single items for psychological distress and self-efficacy, which are taken and adapted with permission from the validated MSK Health Questionnaire (MSK-HQ) [34]:

“How much distress have you been experiencing because of your pain, on average, over the last 2 weeks?” (Responses were recorded on a scale of 0-10, where 0 is no distress and 10 is extremely distress.)

“How confident have you felt about managing your pain by yourself (eg, medication, changing lifestyle)?” (Responses were recorded on a scale of 0-10, where 0 is not at all confident and 10 is extremely confident.)

### Clinician Behaviors via Linked Medical Records

Clinician decision making and behaviors will be examined through a review of the practice computerized medical records for all patients who give consent for this (at the end of the initial questionnaire). This will allow data to be analyzed from (1) individual patient outcomes, (2) the initial patient-clinician consultation electronic template, and (3) further aspects of their medical record over 6 months following the MSK consultation. Variables of interest from the MSK consultation will include the date of consultation, coded reason for the consultation, MSK pain intensity and location, Start MSK Tool (clinician-completed version) individual items and total score (intervention arm only), and information about the management decisions and other actions taken by the clinician. Other clinical behaviors of interest are described in the *Outcomes* section. The information collected on the patient’s risk subgroup and management options in the intervention practices will be audited and fed back to clinicians at regular intervals, allowing them to see how closely they have followed the matched clinical management options. At the end of the trial, we will also report the fidelity of clinicians in the intervention practices in terms of completing the tool and choosing matched treatment options. The template MSK pain intensity score will also provide the initial score for the primary outcome for participants in both arms of the trial.

Physiotherapists treating patients referred from participating practices will complete their usual clinical records. At the end of the trial, we will collect details about the physiotherapy treatment provided for consenting trial participants to compare between intervention and control.

### Practice-Level Anonymized and Aggregated Data of Musculoskeletal Read Codes

Each participating general practice will provide anonymized medical record data from potentially eligible patients for whom the template was activated through entry of an MSK Read code (estimated n ≥5000). We will compare the following:

1. The characteristics of those patients in which the template is activated with those who respond to the initial questionnaire and provide individual-level patient outcomes. The information examined will not involve any patient-identifiable data and will not be linked to any other data unless prior patient consent has been provided.

2. Aspects of clinical behaviors for 6 months following the index consultation to compare intervention and control practices for key treatment processes for each risk subgroup. For example, this will include requests for the following:

Prescriptions (eg, categorized into simple analgesics, nonsteroidal anti-inflammatory drugs, neuromodulators, muscle relaxants, corticosteroid injections, and opioids)Referrals (eg, categorized into physiotherapy/MSK interface services, specialist services including orthopedics, pain clinics, and rheumatology)Imaging (eg, categorized into x-rays/magnetic resonance imaging (MRI) scans, MSK ultrasound scans, and bone density scans)Sick certifications or fit notes (eg, categorized into number per patient and mean length in days)Repeat MSK general practice visits.

The collection of anonymized and aggregated medical record data is not uncommon within similar general practice research studies that examine potential recruitment bias [35] or for intervention studies examining clinician decision making and behaviors during the consultation (eg, the Primary Care Osteoarthritis Screening Trial [28] and the Study of Work and Pain trial [30,36]).

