#### Secondary Objectives

The secondary objectives of the trial were as follows:

1. Examining differences in secondary clinical outcomes, clinical decision making and behaviors, and health economic outcomes at the 6-month follow-up:

Patient outcomes include physical function, confidence in managing their pain (pain self-efficacy), psychological distress, fear-avoidance beliefs, patient-perceived reassurance from their clinician, pain interference with sleep, hobbies/leisure activities, pain interference with work and daily routine, health-related quality of life, and patient satisfaction with care received.Clinical decisions and behaviors of interest include identifying whether stratified care changes the primary care management of MSK patients. We anticipate that primary care clinical management will become more consistent for patients within each risk group and be more in line with stratified care, where patients at low risk of persistent disabling pain are less likely to be referred for additional health care, whereas patients at medium or high risk are more likely to be referred for additional health care in ways that match the recommended management options. Using the practices’ medical record data, we will examine differences between the trial arms in clinical decision making and behaviors.Health economic evaluation will determine the cost-utility of stratified care in comparison with usual, nonstratified care. A cost-consequence analysis will initially be reported, with a subsequent cost-utility analysis from a health care perspective to determine cost per quality-adjusted life years (QALYs) gained, calculated using EuroQol-5D-5L (EQ-5D-5L) responses from the initial and 6-month questionnaires. A broader costing perspective will be considered in a sensitivity analysis, taking into account National Health Service (NHS)/Personal Social Services (PSS) costs and productivity costs associated with time off work. The outcome of interest for the economic analysis will be QALYs. Additional exploratory analyses will consider the cost-effectiveness of stratified care compared with usual nonstratified care for patients at low, medium, and high risk of persistent disabling pain.

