In addition, we have identified a number of a priori potential mediators at the level of clinical behavior, measured using the medical record data, including the proportion of patients who receive prescription medications for MSK pain, referrals to other services (eg, physiotherapy and secondary care specialists), referrals for investigations (eg, radiographs, MRI/Computerized Tomography (CT) scans, blood tests), sick certifications (fit notes), and further MSK-related consultations. We will test if there are significant differences in these behaviors between intervention and control practices and whether any of these differences are associated with the results in terms of patients’ pain intensity.

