### Sample Size

In an average-sized UK general practice (6000 registered adults), we expect that about 800 potentially eligible patients will consult with the MSK pain sites of interest per year or 400 over 6 months. The feasibility and pilot trial showed that, on average, the template was activated 375 times over 6 months in each practice, and clinicians fully completed it in 41.1% (154/375) of cases (6 times per week), leading to a letter inviting the patient to participate in the data collection. From this, we expect that 40% of patients invited will return their initial questionnaire in the main trial, be eligible, and consent to further data collection (or 62 over 6 months in 1 practice). However, to be more cautious, given the general uncertainty in data and in generalizability of pilot estimates, we have conservatively estimated the average number of participants recruited per practice within 6 months in the main trial to be around 33% of those invited (or n=50 in 6 months or n=9 per month per practice).

The trial is powered at 90% to test the hypothesis of the overall superiority of stratified primary care versus usual care based on an alpha of 5% (two-tailed) to detect a small *effect size* (standardized mean difference) of 0.2 [54] in the primary outcome (pain intensity). An effect size of 0.2 was considered to be appropriate based on information from the feasibility and pilot trial, in which the proportion of responders in the 3 risk subgroups was 32% at low risk, 55% medium risk, and 13% high risk. Our previous trial of stratified care for patients with low back pain (the Start Back trial) found an effect size of 0.3 and 0.4 in the primary outcome (back pain–related physical function) in patients at medium and high risk, respectively. Therefore, we have assumed these standardized differences in this new trial [19]. In addition, the minimal clinically important difference for the numerical rating scale (NRS) pain intensity scores in MSK pain has been reported to be 1 point [55], which equates to an effect size of about 0.4, relative to an expected SD of about 2.5 [54]. We expect that there would be little or no difference between stratified care and usual care for patients in the low-risk subgroup. Hence, by multiplying these effects by the expected proportion within each subgroup, the overall effect size of interest is 0.2 (equating to an absolute mean difference of approximately 0.5 in pain intensity on a 0-10 scale).

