### Evaluation of the Process Outcomes

Process outcomes will be evaluated through comparison of aggregated anonymized data at the level of the participating general practices, by examining, for example, reconsultation rates for MSK pain over 6 months and referral rates to other services between practices in the stratified care versus usual care arms. In intervention practices, we will also investigate the proportions of patients for whom the electronic template is completed, and matched clinical management options are selected overall and by risk subgroup.

A descriptive analysis will be undertaken of physiotherapist data by the intervention arm (eg, waiting times, number of treatment sessions, and clinical grade of treating physiotherapist).

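### The anonymised audit cannot give the promised by-risk comparison because unlinked control records hold no risk group, and the remaining referral comparisons are not split by risk although opposite shifts are expected.

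*Protocol article*

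**What the plan says.** All references are to the protocol article.

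- **Objective.** *Secondary Objectives* expects low-risk patients to be referred less often, while "patients at medium or high risk are more likely to be referred for additional health care", in line with the matched options. Differences between arms are to be examined in the practices' medical record data.
- **Audit.** *Practice-Level Anonymized and Aggregated Data of Musculoskeletal Read Codes* covers patients whose template was activated (estimated at least 5000). Its second item is to "compare intervention and control practices for key treatment processes for each risk subgroup", for example prescriptions, referrals, imaging, fit notes and repeat visits. Its first item says the information "will not be linked to any other data unless prior patient consent has been provided".
- **Where risk is recorded.** *Study Design and Setting* gives the control template three questions (eligibility, pain site, pain intensity) and adds the tool in the intervention arm only. *Control Arm* rules out formal stratification tools. *Clinician Behaviors via Linked Medical Records* lists the tool's "individual items and total score (intervention arm only"). Table 1 collects the tool from participants in the initial and 6-month questionnaires, with no restriction by arm.
- **Other behaviour comparisons.** *Process Evaluation*, on clinical behaviours as mediators: "We will test if there are significant differences in these behaviors between intervention and control practices". *Evaluation of the Process Outcomes* compares, as examples, reconsultation rates and "referral rates to other services between practices in the stratified care versus usual care arms". Its only by-risk summary is for intervention practices.

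**The concern.** There are two linked problems. The one dataset large enough for a precise look at clinician behaviour is assigned a comparison that needs a variable its control half does not contain. An analysis plan cannot repair this, because the variable is not collected. What then remains in the text is a set of between-arm rates with no risk split, and for referral these average over changes expected to have opposite signs.

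At stake is a stated secondary objective: whether stratified care moves management in the intended direction in each risk group. If care is reallocated as intended, the overall referral rate may barely move, and a reader could conclude that clinicians did not change. The clinical behaviours are also named as mediators, so the same misreading could carry into the explanation of the trial result. The primary pain outcome is not affected.

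**Working it through.** **Step 1. Can the by-risk audit comparison be made?**

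| Record type | Risk group available? |
|---|---|
| Control, unlinked | No: the template has no tool |
| Intervention, unlinked | Only if the template was completed (154/375 = 41.1% in the pilot) |
| Consenting participants, both arms | Yes: initial questionnaire, plus linked record |

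Linkage would not rescue the rest of the audit, because patients who returned no questionnaire have no self-reported score. The participants are about 1200, against an audit of at least 5000 (1200/5000 = 24%), or against 375 x 24 = 9000 activations at the pilot rate (13%).

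**Step 2. What does an overall rate measure?**

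Inputs from *Sample Size*: 32% low, 55% medium and 13% high risk among pilot responders, so 68% medium or high. Applying this mix to audit records is an assumption. With a fall of x points at low risk and a rise of y points at medium/high risk:

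net change = 0.68y - 0.32x

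- It is zero when x/y = 0.68/0.32 = 2.125. For x = 10, y = 3.2/0.68 = 4.7.
- x = 10, y = 10: 6.8 - 3.2 = +3.6 points.
- x = 10, y = 5: 3.4 - 3.2 = +0.2 points.

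**Step 3. Illustration of the consequence**

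The article states no power for clinician behaviour. Its primary-outcome calculation reproduces and is not in dispute:

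- unadjusted n: 526 per arm (stated 525);
- inflation: [1 + ((1 + 0.65²) x 50 - 1) x 0.01]/0.75 = 1.701/0.75 = 2.27 (stated 2.3);
- deflation: (1 + 5 x 0.7)/6 - 0.5² = 0.50 (stated 0.5);
- adjusted n: 597 unrounded, or 525 x 1.15 = 604 (stated 600).

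The same design effect, 1 + ((1 + CV²)m - 1) x ICC, is now applied to referral with 12 practices per arm. The documents give no referral rates, so these are assumptions: a 30% usual-care rate in every risk group, ICC 0.01 (the article's value for the primary outcome) and CV 0.65. Power is two-sided 5%, counting rejections in the expected direction only, so it tends to 2.5% at no net change.

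| Set | Shifts (low / medium-high) | Overall rate | Low risk alone | Medium/high alone |
|---|---|---|---|---|
| Audit, 2500 per arm | -10 / +10 | 28% | 91%* | 94%* |
| Audit, 2500 per arm | -10 / +5 | 3% | 91%* | 44%* |
| Participants, 600 per arm | -10 / +10 | 18% | 54% | 70% |
| Participants, 600 per arm | -10 / +5 | 3% | 54% | 24% |

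*Only if risk were known for everyone in both arms, which the audit does not provide.

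Over usual-care rates of 20-40% and ICC 0.01-0.05, overall power in the audit is 10-34% for -10/+10 and about 3% for -10/+5.

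**Step 4. The arm by risk-group contrast in participants (same assumptions)**

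- Low risk: n = 0.32 x 600 = 192 per arm, 16 per practice, design effect 1.218, effective n 157.7. SE = √[(0.30 x 0.70 + 0.20 x 0.80)/157.7] = 0.0484.
- Medium/high: n = 408 per arm, 34 per practice, design effect 1.474, effective n 276.9. SE for 30% v 40% = √[(0.21 + 0.24)/276.9] = 0.0403.
- SE of the contrast, treating the groups as independent: √(0.0484² + 0.0403²) = 0.0630.
- For -10/+10: z = 0.20/0.0630 = 3.17, power Φ(3.17 - 1.96) = 89%. For -10/+5: SE 0.0627, z = 2.39, power 67%.
- Over the same ranges of rate and ICC: 56-96% and 35-80%.

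This ignores misclassification of risk by a score taken after the consultation.

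**The case against.** The strongest reply is that this is a one-line wording slip. The linked review of consenting participants joins template, record and questionnaire, so a by-risk comparison between arms is feasible there. The objective refers to medical record data generally, not to the anonymised audit alone. The practice-level rates are offered as examples, and the detailed analysis plan is not shown. Referrals are also categorised by service: the article's own background reports fewer secondary care referrals at low risk and more physiotherapy referral of at-risk patients, and separate categories need not cancel.

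Much of this stands. It rules out several stronger readings that a reader might infer:

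- *That the objective cannot be answered.* It can, in linked participants. But the article states no such contrast. It plans to examine results by risk group for the patient-level mediators, without saying the same of clinical behaviours.
- *That overall rates should be expected near null.* The documents do not support this. Cancellation is exact only near the 2.1 ratio, equal 10-point shifts leave +3.6 points, and the earlier back pain implementation study is reported to have raised physiotherapy referral.
- *That the point extends to prescribing, imaging and fit notes.* Opposite directions are stated as an objective only for referral.
- *That arm by template pain should be the main test.* Its apparent advantage rests on an assumed pain-risk gradient. In simulations of 24 practices with 154 completed templates each, mean pain of 4.5/6.3/7.8 (SD 1.8) by risk group gave it 74-78% power against 13-26% for the overall rate at -10/+10. Those inputs imply a total SD of about 2.1, where the article expects about 2.5. With a weaker gradient (5/6/7, SD 2.2) it gave 26% against 27%. Pain is also available only for completed templates, and completion may differ by arm because the intervention template is longer.

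The reply does not remove the core: the audit comparison as written needs control data that do not exist.

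**Conclusion.** The point holds in limited form. That the by-risk comparison is impossible in unlinked control records follows from the text alone and needs no assumption. That opposite referral shifts can dilute or cancel in an overall rate is arithmetic on the protocol's 32/55/13% mix, assuming the mix carries over from pilot responders. *Can* is the right word: the sizes of the shifts are not in the documents.

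The power figures are illustrations under assumed referral rates, shifts and ICC. They show how far an overall test may miss a reallocation of care, and they are not properties of this trial. The matter concerns a secondary objective and the process evaluation, and is worth correcting because the correction is cheap and the misreading easy.

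**What to change.** 1. In the practice-level audit section, remove the risk-subgroup comparison for unlinked records.
2. Make the test of the referral objective an arm by risk-group contrast in consenting, linked participants of both arms, using the Start MSK Tool from the initial questionnaire and accounting for clustering by practice. State that this score is taken after the consultation (*Secondary Outcomes* allows up to 4 weeks), so allocation may have influenced it, and that precision is lower than in the audit.
3. Report overall audit referral rates by service category (physiotherapy/MSK interface; specialist), and say that a null overall rate does not show unchanged management.
4. Optionally, add arm by template pain for referral as a supportive analysis only, stating that pain is a proxy for risk and exists only for completed templates (41.1% in the pilot).

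Cost: changes of wording and one extra model term, with no new data. The drawback is that the by-risk answer rests on about 1200 participants rather than on the full audit.
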